#### Influenza vaccination programme cost

The financial and economic costs associated with the vaccination programme will be assessed through the utilization of the World Health Organization’s Seasonal Influenza Immunization Costing Tool (SIICT) [64]. The WHO SIICT was updated in 2020 and was newly named “The WHO Flutool Plus” [64]. The newly developed WHO Flutool Plus enables the estimation of costs associated with various vaccination activities, including microplanning, procurement, distribution, training, social mobilization, service delivery, supervision, and the acquisition of supplemental cold chain equipment [64]. We will customize the Flutool Plus as required to estimate the cost of our facility-based vaccination programme. During the vaccination campaign, icddr,b research personnel will keep track of all cost components of the influenza vaccine campaign. The cost components of the vaccination campaign at the facility level that will be recorded are shown in Table 4.

**Table 4 Tab4:** Cost components of the facility-based piloted influenza vaccination campaign

Dimension	Components of costs

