### Data collection to determine vaccination cost-effectiveness

#### Vaccination campaign

To record health outcomes after influenza vaccination, in one of the two public tertiary-level study hospitals, we will conduct an influenza vaccination campaign before the influenza season, where the vaccine will be offered free of cost to high-risk patients, and in the second hospital, vaccination will not be offered. We will work with the hospital administration to set up a vaccination booth on the hospital premises. Vaccines will be made available at the vaccination booths. Posters and leaflets containing information on influenza vaccination will be displayed at the vaccination booths and key hospital locations with information on the vaccination. Inpatients and outpatients of all departments will be informed about the ongoing immunization campaign. Eligible patients will be offered to take the vaccine during the vaccination campaign. Benefits, significance, adverse effects, and how to manage them will be explained to the patients. Nurses/ Health Assistants (HA) will provide influenza vaccination throughout the campaigns. At 8 AM, the vaccination booth will open and close at 2 PM, six days a week throughout the campaign period. A vaccination card will be issued to the participants. All high-risk groups will get one dose of seasonal influenza vaccination (Quadrivalent), except children aged six months to 8 years, who will receive two doses four weeks apart [31, 32]. All vaccines will be the southern hemisphere vaccine as recommended by the WHO for Bangladesh. Regarding children, we will make phone follow-ups with the guardians of the children receiving the first dose to remind them about the second dose schedule, and it will be recorded in the vaccine card if the second dose is received. In order to ensure the availability and quality control of vaccines throughout the three-month campaign period, the research team at icddr,b will closely monitor the campaign. All vaccinated participants will receive notification regarding potential adverse events following immunization (AEFI) during the vaccination process. To document any untoward occurrences after Adverse Events Following Immunization (AEFI), we will adhere to the pre-existing surveillance mechanism implemented by the World Health Organization (WHO) and the Ministry of Health and Family Welfare (MoHFW) of the government of Bangladesh. During the vaccination campaign briefing session in each study hospital, participants will be informed about the process of reporting any Adverse Events Following Immunization (AEFI) within the hospital’s established surveillance system. Additionally, participants will be provided with the mobile number, as stated in the consent form, to report any such issues. Furthermore, during the vaccination campaign implementation, a representative from icddr,b will be assigned to each study hospital to oversee and monitor any adverse events following immunization (AEFI) in conjunction with the hospital’s existing surveillance system. If an Adverse Event Following Immunization (AEFI) case is identified, the personnel affiliated with icddr,b will promptly notify the Hospital Surveillance Officer (HSO), provide support to the HSO in completing the AEFI report form, and subsequently transmit it to the Expanded Programme on Immunization (EPI) headquarters via the Chief Health Officer.

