### Direct medical and non-medical costs for influenza illness episodes

Direct costs will consist of health care provider fees, hospital registration fees, bed rental, prescriptions, laboratory testing, transportation, and mobile phone calls. We will also record informal payments made during hospital visits. All medications, laboratory tests, registration, and room rental costs will also be included. We will also collect payment if patients visit a pharmacy or other clinics prior to hospitalization. The non-medical expenses for patients or caregivers include food, lodging, and transportation. Our field staff will collect data directly from patients and their families. Members of the participant’s family or the participants themselves will be able to determine the drugs and tests they received at no cost due to hospital subsidies and those for which they incurred personal expenses (out-of-pocket).

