### Productivity loss or indirect cost

We will also collect data on participants’ or caregivers’, or family members’ lost productivity and indirect costs incurred during illness. We will record the number of workdays missed by participants’ family members, participants themselves, and caregivers due to sickness or family caregiving. We will exclude weekends and national holidays from our calculation. Every day missed due to illness or the need to care for sick family members will be considered a forfeited workday for hourly-wage workers and housewives. We will not consider the days missed due to decreased activity, such as a partial work day, absences from school, or fatalities caused by influenza. The number of productive days lost due to influenza-related fatalities will be estimated based on the baseline mortality rate. This will be multiplied by the median daily wage in Bangladesh, followed by an adjustment based on the prevailing unemployment rate in the country.

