**Recurrent or operational costs**	
Procurement of vaccines and injection supplies	• Cost of vaccines and injection supplies, regardless of the source of financing • Cost of freight, clearance, insurance, and taxes
Service delivery	• Value of personnel time spent on vaccination • Transport fuel • Personnel per diems to travel to vaccination sites • Supplies– e.g. cotton
Monitoring and evaluation	• Tally sheets or registers • Pens and pencils • Vaccination cards • Materials for vaccine booths
Supervision	• Value of personnel time spent on supervision • Travel allowances • Transport fuel and maintenance • Stationery
Waste management	• Purchase of incinerators (annualized/discounted) • Fuel • Transport

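### Household costs are collected for influenza illness but not for vaccination, so if illness costs enter the ICER as costs averted, the child ICER is biased toward vaccination

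*Protocol article*

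**What the plan says.** **Vaccination side.** The section Influenza vaccination programme cost says that "icddr,b research personnel will keep track of all cost components of the influenza vaccine campaign", and then: "The cost components of the vaccination campaign at the facility level that will be recorded are shown in Table 4". Table 4 lists micro-planning, training, social mobilization, procurement, service delivery, monitoring, supervision, waste management and cold chain. The time and travel items under service delivery are those of staff: "Value of personnel time spent on vaccination" and "Personnel per diems to travel to vaccination sites". No row covers the fares, food or time of the person vaccinated or of a guardian.

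**Illness side.** The section on direct medical and non-medical costs states: "The non-medical expenses for patients or caregivers include food, lodging, and transportation". The section on productivity loss adds lost time for participants, family members and caregivers: "Every day missed due to illness or the need to care for sick family members will be considered a forfeited workday". Study design assigns the direct and indirect illness costs to the cost-effectiveness objective.

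**Schedule.** Under Vaccination campaign, all groups get one dose, "except children aged six months to 8 years, who will receive two doses four weeks apart". Table 3 recruits people who are attending the hospital for routine care.

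**ICER.** Cost-effectiveness estimation defines it as incremental cost over incremental DALYs and judges it against three times GDP per capita. That section names no costing perspective.

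**The concern.** A cost-effectiveness ratio needs the same perspective on both sides of the numerator. Here a family's bus fare and lost day are collected when the child has influenza, but not when the child is brought back for vaccination.

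The first dose is offered at a visit that is already being made, so it adds little household cost in any group. The second dose, four weeks later, will normally need a separate trip to a tertiary hospital with a guardian. Only children have that visit, so the gap falls mainly on one risk group. It can therefore affect both the child ICER and its comparison with the other groups' ICERs, which are meant to inform national policy.

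**Working it through.** The plan states no ICER or programme cost, so there is no figure to reproduce. The check covers direction first, then scale.

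**Direction.** If household illness costs are included as costs averted, then per vaccinated child

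ICER = (programme cost + adverse-event cost − illness cost averted) / DALYs averted.

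Let c be the household cost of the second-dose visit. Leaving out c lowers the ICER by c / (DALYs averted per child). For any c above zero, the reported child ICER is too low.

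**Inputs for scale.**
- ILI proportion in children: 15.30% (sample size for vaccine effectiveness).
- Expected efficacy: 50% to 81% (same section), applied here to ILI.
- Direct cost of influenza illness, children under five: US$70 (sample size for the cost-components survey).
- Household cost of one second-dose trip: not in the document; assumed US$0.5 to 2.
- Return for dose 2: assumed to be every child.

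**Children vaccinated per ILI case averted** = 1 / (ILI risk × efficacy)
- Efficacy 50%: 1 / (0.153 × 0.50) = 13.1
- Efficacy 81%: 1 / (0.153 × 0.81) = 8.1

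**Household cost left out per ILI case averted** = that number × c

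| Efficacy | c = US$0.5 | c = US$2 |
|---|---|---|
| 50% | 6.5 | 26.1 |
| 81% | 4.0 | 16.1 |

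The range is about US$4 to 26.

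**Share of the direct cost averted**, if every averted ILI case would have cost US$70
- Lowest: 4.0 / 70 = 6%
- Highest: 26.1 / 70 = 37%

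The same result per vaccinated child: direct cost averted is 0.153 × 0.50 × 70 = US$5.35 at 50% efficacy and 0.153 × 0.81 × 70 = US$8.68 at 81%. Then 2 / 5.35 = 37% and 0.5 / 8.68 = 6%.

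**Shift in the ICER.** DALYs averted per vaccinated child are not given. Over an assumed 0.0005 to 0.01, the shift runs from 0.5 / 0.01 = US$50 to 2 / 0.0005 = US$4,000 per DALY. That range only shows how little the document settles.

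**Valuing guardian time.** The productivity section leaves out days of reduced activity, such as a partial work day. The booth is open from 8 AM to 2 PM. A second-dose visit that takes less than a full workday would be valued at zero under that rule, so copying it across would leave mainly fares and food.

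**The case against.** **Table 4 is limited to the facility level, and the article condenses a fuller protocol.** Perspective and questionnaire items could sit in that fuller document, and the costing tool is to be customised. This does not remove the point. Table 4 is an itemised statement of what will be recorded, not a silence, and the programme activities named alongside it include no household item.

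**The ICER numerator is not itemised.** The article relies on built-in formulas of a costing tool and lists productivity loss averted among additional outputs after the ICER. This stands. The bias is conditional on household illness costs entering the numerator, although Study design points that way.

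**The scale is assumed.** This also stands. The trip cost is not in the document, and not every child will return. The US$70 excludes ages five to eight and indirect costs, and its mix of care settings is not stated.

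Four stronger readings are tempting but unsupported:
- *Reminder calls are left out as well.* The plan says "we will make phone follow-ups with the guardians of the children receiving the first dose to remind them about the second dose schedule". The study team makes these calls, so they are a programme cost. They may fall under personnel time or under the promise to track all campaign components. Table 4 has no telephone line, but omission is not established.
- *The omission equals or exceeds the illness cost averted.* The Background implies US$108 million / 25 million = US$4.32 per outpatient visit, against which US$4 to 26 would be 0.9 to 6 times. That figure covers all ages in 2010, outpatient care and direct cost only. The US$70 is closer to the study's child group and is the plan's own planning figure.
- *A completed two-dose schedule is credited to the programme while its cost is not.* Neither the coverage section nor the efficacy section says that the second dose defines a vaccinated child.
- *The cost-effectiveness conclusion would change.* The document gives no programme cost, DALYs averted or GDP figure, so this cannot be shown.

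**Conclusion.** The asymmetry is real: Table 4 has no household item, while illness costing includes household travel, food, lodging and lost workdays. If those illness costs enter the ICER as costs averted, the child ICER is biased in one direction, toward vaccination, and more than the ICERs of the one-dose groups.

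The size is indicative only. It rests on the assumed trip cost, full return for dose 2, the plan's ILI proportion and efficacy range, and US$70 per averted case. On these, the omission is about 6% to 37% of the direct cost averted. Actual return below 100% or a routine visit that coincides with dose 2 would reduce it; averted cases cheaper than US$70 would raise the share. The plan should correct this, but nothing in the document shows that it would reverse the three-times-GDP conclusion.

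**What to change.** 1. State the costing perspective under Cost-effectiveness estimation, say which illness costs enter the ICER numerator, and apply that perspective to both illness and vaccination.
2. For the household-inclusive ICER, add a recipient and caregiver row to Table 4: fares, food and guardian time for the second-dose visit, and any extra time at the first dose.
3. Collect these with two or three questions at the second dose or in a follow-up call already planned. If the campaign is over, use fares from the cost survey as a proxy, with a sensitivity range.
4. Value guardian time in hours or part-days, or apply one stated partial-day rule to both illness and vaccination. The present exclusion of partial workdays would otherwise set most of it to zero.
5. If a provider-perspective ICER is also reported, leave household costs out of both sides.

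The cost is a few form items and one line in the costing sheet. The child ICER will become slightly less favourable to vaccination.

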**Start-up cost**	
Micro-planning	• Personnel time spent in meetings • Per diems and travel allowances • Venue rental • Transport
Training	• Value of personnel time spent on training • Development of training materials • Per diems and travel allowances • Venue rental • Transport • Training materials • Stationery
Social mobilization/IEC	• Value of personnel and volunteer time spent on material development and other activities • Facilitator time in meetings • Per diems and travel allowances • Stationery • Printing of posters and leaflets • Production of TV and/or radio spots
**Recurrent or operational costs**	
Procurement of vaccines and injection supplies	• Cost of vaccines and injection supplies, regardless of the source of financing • Cost of freight, clearance, insurance, and taxes
Service delivery	• Value of personnel time spent on vaccination • Transport fuel • Personnel per diems to travel to vaccination sites • Supplies– e.g. cotton
Monitoring and evaluation	• Tally sheets or registers • Pens and pencils • Vaccination cards • Materials for vaccine booths
Supervision	• Value of personnel time spent on supervision • Travel allowances • Transport fuel and maintenance • Stationery
Waste management	• Purchase of incinerators (annualized/discounted) • Fuel • Transport
**Capital costs**	
Cold chain equipment	Cold chain equipment (annualized and discounted)

### Data sources for determining the required capacity of facility-based influenza vaccination

We will estimate the required capacity of the seasonal influenza vaccination programme based on the cold chain capacity requirements of the hospitals. We will also collect secondary data to calculate requirements at each hospital.

Secondary data will be collected about the population size of the targeted risk group in the hospital’s catchment area, the number of doses required for vaccinating each high-risk individual, the number of doses per vial, packed volume, doses syringes, and safety box [26–30]. Table 1 represents the assumptions on the population size of the targeted risk group in the catchment area.

## Study size

### Sample size and sampling

#### The sample size for the vaccine acceptability objective

Our study design will be quasi-experimental. Our primary outcome for vaccine acceptability is the intention to receive the influenza vaccine. Based on studies utilizing the high-risk group-specific health belief model conducted in neighboring countries, it has been found that 91% of elderly people, 88% of adults with chronic illness, 76.3% of pregnant women, and 62.4% of parents with six to three-year-olds expressed their intention to get the influenza vaccine [38–40, 45]. We expect a similar positive intention to receive the influenza vaccine, ranging from 62 to 91% for our target study population. In this study, we employed a significance level of 5%, a power of 80%, a design effect of 1.2, and account for a non-response rate of 10% to determine the required sample size [65–67]. We will utilize a validated health belief model tool. To avoid selection bias, we will use random assignment to the study based on predefined inclusion and exclusion criteria. We will also provide training to study staff about random enrolment of the study participants based on inclusion and exclusion criteria. Table 5 represents the estimated sample size by the high-risk group for the vaccine acceptability objective.

**Table 5 Tab5:** Estimated sample size for investigating the vaccine acceptability/ intention to receive, health outcome due to vaccination, and cost-effectiveness of implementing a facility-based influenza vaccination

High-risk group	The sample size for the vaccine acceptability survey	The sample size for vaccine effectiveness	The sample size for the cost-components survey
Children 6 months to 8 years	659	465	60
Pregnant women	495	756	39
Elderly ≥ 60 years	330	736	56
Adults with chronic diseases	425	610	31

#### The sample size for the vaccine effectiveness objective

Our primary outcome for health outcome for vaccination is vaccine efficacy against influenza among high-risk group populations. Studies from neighboring countries found that ILI symptoms were 15.30% of children, 31.23% of adults with chronic illness, 10.97% of pregnant women, and 20% of the elderly [68–70]. A systematic review of seasonal influenza vaccine policy, use, and effectiveness also revealed that pooled vaccine effectiveness for high-risk groups in the tropics and subtropics ranged from 48 to 88% (10). We expect a similar vaccine efficacy between 50 and 81% for our study’s targeted high-risk group population. A 5% significance level, 80% power, design effect 1.2, and 10% non-response were used to calculate the required sample size to estimate vaccine effectiveness [65–67]. Table 5 represents the high-risk group’s estimated sample size for vaccine effectiveness.

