### Study setting

We selected study hospitals considering several factors. Firstly, we will use the hospital-based influenza surveillance (HBIS) platform to conduct this study. We have chosen Rajshahi Medical College Hospital and Khulna Medical College Hospital for our study activities on high-risk groups’ vaccine acceptability and cost-effectiveness. We will enroll Severe acute respiratory illness (SARI) and influenza like illness (ILI) patients identified from the HBIS platform to meet our study objectives. We will also collect influenza virus test results from the HBIS platform and data on influenza illness episodes’ costs from the influenza-positive SARI and ILI patients. This approach will save influenza virus testing costs not allocated in the current study budget. Secondly, to assess the outcome of influenza vaccination, we plan to enroll patients from public tertiary-level hospitals (one treatment/vaccinated and the other control hospital) to minimize baseline differences between the treatment/vaccinated and control arm. Thirdly, we have chosen Ragib-Rabeya Medical College & Hospital to represent public and private healthcare facility cost differences while estimating the costs of influenza illness. A brief description of the study sites’ bed occupancy rate and average monthly admission are represented in Table 2 [29, 30].

**Table 2 Tab2:** Demographic characteristics of the study hospitals

Study sites	Bed occupancy rate (%)	Total no OPD visits	Total number of PNC visits	Total number of admission	Middle wealth quantile
Rajshahi Medical College Hospital	198.05	114,818	2,405	22,022	24.1%
Khulna Medical College Hospital	275.00	35,311	991	8,859	24.8%
Jalalabad Ragib-Rabeya Medical College & Hospital	NA	NA	NA	NA	15.8%

Source: Local health bulletin October 2022

OPD = outpatients care department; PNC = post-natal visit

Note: a bed occupancy rate greater than 100% indicates that these hospitals receive and care for more patients than their capacity

Study sites for influenza vaccine acceptability, health beliefs, barriers:

We will conduct a health belief model (HBM) survey in two conveniently selected hospitals:

Rajshahi Medical College Hospital, Rajshahi.Khulna Medical College Hospital, Khulna.

Study sites for influenza vaccination cost-effectiveness objective:

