### Variables

We thoroughly reviewed the literature on different outcome variables and explanatory factors in our research [5, 31, 36–44]. Regarding our first objective, which centered on vaccine acceptability, our primary outcome of interest wil be the high-risk groups’ intention to receive the influenza vaccination. This will assist us in assessing the propensity of high-risk groups’ willingness to receive influenza vaccine. Our second objective focuses on vaccination effectiveness, precisely measuring vaccine efficacy against influenza in high-risk group groups. This metric will enable us to assess the efficacy of the vaccination in protecting high-risk group groups. In addition, we will thoroughly examine the cost components related to influenza, focusing on the overall costs of influenza-related illnesses in high-risk groups as our second objective’s variables. To understand the complex factors that affect vaccine acceptance and effectiveness, we will examine various explanatory variables, including age, gender, occupation, location, marital status, and income, among others.

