### Follow-up of vaccinated and unvaccinated participants

icddr,b field staff will follow up with vaccinated and unvaccinated study participants bi-weekly through mobile phone for the entire influenza season. During the follow-up, data will be recorded on health outcomes, including respiratory symptoms, influenza-like illness, hospitalization, and death. To minimize loss to follow-up, icddr,b field team will contact the cohort member at their convenience. icddr,b field team will use the alternative number collected during enrolment where they cannot reach their regular mobile phone number. At the end of one follow-up interview, the interviewee will be consulted about the convenient time of their upcoming follow-up date. After taking these approaches, if it is impossible to reach a cohort member for three follow-up schedules, he/she will be declared lost to follow-up case. For the loss to follow-up case, icddr,b field team will place notes on their data identification number. The study flow chart is shown in Fig. 2.

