#### Data sources for estimating influenza-associated disease burden

To estimate the key parameters of influenza-associated disease burden, such as the number of outpatient visits, hospitalization, and deaths, we will collect data from secondary sources [17, 26, 31, 34, 35, 54–58]: Table 1 represents the assumption and secondary data sources by each target risk group.

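### The effectiveness outcome is named as efficacy against influenza, but cohort follow-up records only untested illness, so the plan estimates an ILI effect and its 80% power is conditional

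*Protocol article*

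**What the plan says.** The section on sample size for the vaccine effectiveness objective sets the outcome: "Our primary outcome for health outcome for vaccination is vaccine efficacy against influenza among high-risk group populations". The Variables section repeats it: "precisely measuring vaccine efficacy against influenza in high-risk group groups".

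The section on follow-up of the two cohorts describes the data: "icddr,b field staff will follow up with vaccinated and unvaccinated study participants bi-weekly through mobile phone for the entire influenza season", and then "During the follow-up, data will be recorded on health outcomes, including respiratory symptoms, influenza-like illness, hospitalization, and death". The Abstract and the Study design section list ILI, hospitalization and death only. None of these places mentions a specimen or a laboratory result.

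Virus tests appear in the Study setting section. Results are taken from the hospital-based influenza surveillance (HBIS) platform, in connection with enrolled SARI and ILI patients and the costs of their illness, with the comment: "This approach will save influenza virus testing costs not allocated in the current study budget".

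The planning event rates are ILI rates: "Studies from neighboring countries found that ILI symptoms were 15.30% of children", followed by 31.23% (chronic illness), 10.97% (pregnant women) and 20% (elderly). The expected vaccine efficacy is 50-81%. Other inputs are 5% significance, 80% power, design effect 1.2 and 10% non-response. Table 5 gives 465 children, 756 pregnant women, 736 elderly and 610 adults with chronic disease.

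The section on vaccine efficacy estimation, placed under the cost-effectiveness analysis, forms VE as (1 - RR) x 100 by Poisson regression without naming the event counted. Burden inputs come from secondary sources: "To estimate the key parameters of influenza-associated disease burden".

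**The concern.** The named outcome needs influenza status for each illness, and the follow-up does not collect it. No later analysis plan can recover a status that was never recorded. Followed as written, the study would report an effect on all-cause ILI under the label of efficacy against influenza.

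The Background section says that influenza antibodies give little or no protection even against other influenza types or subtypes. An effect on ILI caused by other pathogens therefore cannot be assumed, and the ILI effect will be smaller than the influenza effect unless nearly all ILI is influenza. Two things follow. The study may lack the power it claims for the comparison it can make. And a diluted VE may be carried into an economic model built on influenza-associated visits, admissions and deaths, making the vaccine look less useful to the policy bodies that the article addresses.

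**Working it through.** **1. Can cohort data give influenza status?** Outcome: influenza. Recorded in the cohorts: symptoms, ILI, hospitalization, death, by telephone. Tests: surveillance SARI/ILI patients only, with no testing budget. Linkage of cohort members to surveillance results: not described. The estimable quantity is therefore VE against an untested event, in practice ILI.

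**2. Reproducing Table 5.** Pooled two-proportion formula, 1:1, two-sided 5% (sidedness is not stated), 80% power, p2 = p1 x (1 - VE), times 1.2, with non-response as x 1.1 or / 0.9.

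- Read as totals: children fit VE of about 60% (467-472 against 465) and pregnant women about 57-58%. The elderly and chronic-disease figures would need about 43% and 36%, outside 50-81%. At VE 50% the formula gives totals of 525-531 (stated 736) and 304-307 (stated 610).
- Read per arm: the implied VEs are about 45%, 42%, 31% and 26% (children, pregnant, elderly, chronic), all below 50%.

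Neither reading reproduces the whole table from the stated inputs, and the table does not say which reading is meant. Both are carried below.

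**3. Dilution.** Let f be the influenza share of recorded ILI, and assume no effect on other ILI. Then

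VE on ILI = f x VE on influenza, and p2 = p1 x (1 - f x VE).

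f is not in the article. For VE 50-81%, the VE seen on ILI is 15-24% at f = 0.3 and 25-41% at f = 0.5.

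**4. Power on ILI.** Effective n per arm = N x 0.9 / 1.2 (per arm), or half of that (total). Power = Φ((d - 1.96 x se0) / se1), where d = p1 - p2 and se0 and se1 are the pooled and unpooled standard errors. This two-proportion test stands in for the Poisson model.

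Example, chronic disease, per arm, VE 81%, f = 0.3: n = 610 x 0.9 / 1.2 = 457.5; p1 = 0.3123; p2 = 0.3123 x (1 - 0.243) = 0.2364; d = 0.0759; se0 = 0.0295; se1 = 0.0294; (0.0759 - 0.0578) / 0.0294 = 0.615; power 73%.

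Power, in the order children / pregnant / elderly / chronic:

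| f | VE | N as total | N per arm |
|---|---|---|---|
| 0.3 | 50% | 9 / 10 / 15 / 20% | 14 / 15 / 25 / 35% |
| 0.3 | 81% | 17 / 19 / 32 / 44% | 30 / 33 / 56 / 73% |
| 0.5 | 50% | 18 / 20 / 34 / 47% | 32 / 35 / 59 / 76% |
| 0.5 | 81% | 42 / 47 / 74 / 88% | 71 / 76 / 96 / 99% |
| 1.0 | 50% | 61 / 66 / 91 / 98% | 89 / 92 / >99 / >99% |

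The smallest VE on ILI detectable with 80% power is 60 / 58 / 43 / 37% (total) or 45 / 43 / 32 / 26% (per arm). Power reaches 80% only where f x VE is at least this large.

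**5. Economic model.** Influenza cases averted are proportional to influenza burden x VE on influenza. Using VE on ILI instead gives burden x f x VE, which is too small by a factor of 1/f: 2-fold at f = 0.5, 3.3-fold at f = 0.3.

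**The case against.** The strongest reply concerns what is built on the mismatch.

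- **f is unknown.** A reader might infer that the 80% power simply is not delivered. The article does not support that. At VE 81% with Table 5 per arm, the chronic group has 86% at f = 0.35 and the elderly 82% at f = 0.40. With VE only 50%, all four groups keep 80% per arm once f is about 0.9. Follow-up confined to the influenza season, as the follow-up section has it, would favour a higher f than the one-year follow-up stated in the Abstract, Study design and Discussion. The Background rate of 100-170 per 1,000 is a population rate and cannot serve as f. This objection stands, and the power result must be stated as conditional.
- **The 50-81% may not be VE against influenza.** The article cites pooled effectiveness without naming its endpoint. If that was ILI, the planning inputs match and the dilution falls away. The outcome would still be misnamed.
- **The model input is not stated.** A reader might infer that a diluted VE certainly enters the model with a several-fold understatement. The Study design section and the placement of the VE analysis imply that the cohort VE is used, but no text says so or rules out an adjustment, and the fold is only 1/f for an assumed f.
- **HBIS results might be used for the cohorts.** The Study setting section enrols surveillance patients for the study's objectives in general, so this is not excluded. It is not described either, and an illness reported by telephone without attendance at a surveillance hospital yields no specimen.

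**Conclusion.** The point holds as an inconsistency between the named outcome and the data collected: the plan would report effectiveness against untested ILI as efficacy against influenza. That part rests on the text alone.

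The loss of power is conditional on f, on the 50-81% being VE against influenza, on no effect against other ILI, and on how Table 5 is read. At f = 0.3 every group is below 80% under both readings. At f = 0.5 every group is below 80% for VE 50%; for VE 81% only the chronic group (totals), or the elderly and chronic groups (per arm), reach it. The understatement of cases averted by 1/f applies if the cohort VE is entered unadjusted against influenza-associated burden, which the article implies but does not state.

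**What to change.** 1. Name the primary outcome vaccine effectiveness against ILI. Count events in the period of influenza circulation, with the same calendar risk window in both hospitals.
2. Replace the 80% power statement with the power for the ILI effect over a stated range of f and VE. Say whether Table 5 is per arm or total.
3. In CETSIV and the Markov model, pair ILI VE with ILI burden. Use influenza VE = ILI VE / f with influenza-associated burden only as a sensitivity analysis that carries the uncertainty in f. Note that positivity in hospital surveillance may differ from that of ILI reported by telephone, and that dividing by f widens the interval.
4. Optionally, link cohort identifiers to existing HBIS results as an exploratory outcome. State that capture is incomplete and depends on site, which matters with one hospital per arm.

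The cost is protocol wording, one extra model input and, if chosen, a record linkage; no extra patients or tests. The downside is that the stated power becomes less favourable and the effectiveness claim is limited to ILI.
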